#### Skin prick testing

Before testing, we will confirm that participants have not taken short-acting antihistamines within the past 48 h or long-acting antihistamines within the past 7 days. All SPTs will be conducted using Allergopharma and Lofarma extracts (available from Diagenics, Milton Keynes, UK), along with positive (histamine 0.1%) and negative control (50% glycerol, 50% buffered saline) solutions. Tests will be performed on the inside of the forearm on eczema-free areas (for participants with AD). A small drop of the control solutions and each allergen solution will be applied to the skin, and the surface will be pricked through each drop using a sterile, single-use lancet (Allegropharma, available from Diagenics). Skin test sites will be measured after 15 min. The wheal and flare will be measured after 15 min by recording their widest diameters and its perpendicular measurement, and the mean measurement will be recorded.

If the negative control produces a wheal ≥3 mm, we will reschedule the test after 7 days. If the positive histamine control produces a wheal ≤3 mm, then the test will be repeated immediately. Should the repeat result remain ≤3 mm, the test will also be rescheduled after 7 days.

#### Cytokine analysis

To measure the cytokines within the ISF samples, a multiplex kit [Meso Scale Diagnostics™ (MSD), Rockville, MD, USA] will be used. The assay will be conducted in 96-well plates. The plates will be washed three times with the supplied wash buffer prior to use. The multianalyte lyophilized calibrators from MSD will be reconstituted in 1000 μL of Diluent 41 (supplied with the kit). Subsequent standards will undergo a fourfold serial dilution. After washing the plates, 50 μL of sample or standard, based on the plate layouts, will be added to the plate. The plates will be sealed and incubated with shaking (700 rpm) at room temperature for 2 h. Following this incubation, the plates will undergo three additional washes with 150 μL of the washing buffer. Subsequently, 25 μL of antibody solution will be added to each well, followed by incubation with shaking (700 rpm) for 2 h at room temperature. Subsequently, the plates will be washed three times with 150 μL of the washing buffer. Finally, 150 μL of the read buffer solution will be added to each well, and the plates will be immediately placed in the MSD Meso Quickplex SQ 120 machine. The detection antibodies in the plate are equipped with labels that emit light when electrically stimulated by carbon electrodes at the bottom of each well. Data analysis will be performed using MSD Mesoscale Discovery Workbench™ 4.0 software, yielding the concentration of each cytokine in pg mL^–1^ for each well.

#### Basophil and mast cell activation test measurements

For the basophil activation test (BAT), whole blood collected from participants allergic to peanuts as part of an ongoing study will be stimulated with the ISF samples, peanut extract or controls in parallel, and basophil activation will be measured as the proportion of CD63-positive basophils by flow cytometry. For the mast cell activation test (MAT), a human mast cell line called ‘Laboratory of Allergic Diseases 2’ (LAD2) cells will be sensitized with plasma from participants allergic to peanuts, mimicking the participants’ own mast cells, and subsequently stimulated with ISF samples, peanut extract or controls, and mast cell activation will be measured by flow cytometry as proportion of CD63-positive LAD2 cells. Biologic activity and allergenicity will be determined by the ability of peanut proteins present in the ISF samples to induce CD63 upregulation compared with standard peanut extract tested in parallel and controls.

### Endpoints

The primary endpoint will be the change from baseline in inflammatory cytokine concentrations (interferon-γ, IL-10, IL-12p70, IL-17, IL-1β, IL-2, IL-4, IL-6 and tumour necrosis factor-α) in skin ISF following regular massage with a peanut protein-containing extract.

The secondary endpoints will be the potential detection of peanut protein components in retrieved skin ISF. If detected, we will also measure whether the retrieved peanut protein can activate mast cells and basophils, comparing the study arms. Raised TEWL will also be a secondary endpoint.

### Sample size

Our previous studies indicate that the coefficient of variation of ISF cytokines from ISF is ∼20%, peanut protein in skin samples is ∼8% and BAT/MAT from ISF ∼30% (unpublished data). In all these cases a group size of 15 will provide over 90% power to detect a doubling of concentration levels. Allowing for approximately 8% dropout, 65 participants will be needed in the healthy skin and AD groups (130 total).

### Participant recruitment, data collection methods and timeline

We anticipate that study recruitment will take a year, utilizing a broad range of methods, including social media posts and collaborations with our national patient partner organizations Allergy UK and the National Eczema Society.

Individuals expressing interest are prompted to contact the study team through email, upon which they are sent the ­participant information sheet. Screening of interested individuals is conducted via a phone call. Once eligibility is confirmed, potential ­participants are booked in to obtain consent, for a SPT and their baseline visit, if eligible to take part. Participants will be required to attend two study visits in total, 4 weeks apart. The duration of the intervention per participant will be 4 weeks.

A comprehensive and detailed medical history will be recorded at baseline, including age, ethnicity, any existing skin diseases and concomitant medication. If the individual has AD, disease severity will be determined with the objective SCORing Atopic Dermatitis (SCORAD) index. TEWL readings and SPT results to peanut will be recorded. Skin ISF samples will also be taken, and information on the samples will be recorded. Assessments at baseline will be repeated at week 4 (visit 2; Figure 2).

**Figure 2 vzag046-F2:**
[figure not shown]
Schematic diagram showing the participant recruitment timeline. AD, atopic dermatitis; SCORAD, SCORing Atopic Dermatitis.

Participants will be sent a daily record survey electronically through the REDCap database system, enabling the study team to monitor compliance with the study intervention, reinforced through weekly reminder text messages.

To support participant retention all study participants will be offered additional SPT testing to common aeroallergens, including house dust mite, tree pollen, grass pollen, horse, cat and dog. This optional testing will be available to participants only at week 4, during visit 2.

### Allocation

To ensure an even split between the 8 intervention groups, a total of 65 healthy adult volunteers and 65 adults with AD will be randomized 1:1, using block randomization through a code generated by an independent statistician. This computer-generated randomization sequence will be built into the custom-made REDCap database prior to study recruitment. Randomization of participants will be done at the end of the baseline visit by the clinical study team who will have access to the REDCap database.

### Masking

The clinical study team conducting study visits and assessments will not be blinded and will be aware of the participants’ assigned intervention groups. However, laboratory staff responsible for analysing the collected samples will remain blinded to group allocation throughout. Samples provided to the laboratory staff will be anonymized and labelled only with the unique participant identification (ID), date of collection, sample type and study timepoint.

### Data management

The clinical study team will be responsible for data collection under the supervision of the Chief Investigator. Study data will be collected on paper-based case report forms (CRFs) and will be entered into the REDCap database. The daily record surveys completed by participants will be entered directly into the database by them.

All study participants will be allocated a unique study identification number. Participant data collected on paper-based CRFs will be securely stored in a locked room. Data entered into the REDCap database will be securely stored on the King’s College London server. The database will be password protected, and access will be restricted to named study individuals only.

Copies of protocols, CRFs, physiological test results, correspondence, informed consents and other documents relevant to the study will be kept on file by the Chief Investigator’s team at King’s College London and retained for at least 15 years.

### Statistical methods

Comparison of baseline demographic characteristics of study participants across all eight intervention groups will be done using descriptive methods. Adherence to the intervention, including the reasoning behind noncompliance, withdrawal from the study and loss to follow-up, will be summarized. Any adverse events reported by study participants through the daily record surveys or within the visits will also be summarized.

Descriptive and inferential methods will be used for the main analysis. The primary analysis will comprise analysis of covariance to estimate the difference in concentration of inflammatory cytokines in skin ISF between massaging and no massaging patients as per the primary objective by intention-to-treat at week 4. The terms in the model will include the effects of having impaired skin, use of barrier-enhancing cream and massage. Covariates such as gender, ethnicity, baseline TEWL and baseline values of the outcome will be included, with TEWL considered a key mediating factor. Secondary outcomes, including the effect of impaired skin, use of barrier-enhancing cream, and basophil and mast cell activation, and peanut-specific IgE levels, will be analysed similarly. Interaction effects, including those involving massage frequency (categorical and continuous), will also be tested, with significance levels set at 5% for main effects and 10% for interactions. Analyses will account for non-normal data using transformations or nonparametric tests like the Wilcoxon–Mann–Whitney test.

The proportion of participants lost to follow-up after randomization will be summarized in each intervention group. This ­summary will include reasons for loss to follow-up including ­participant withdrawal, withdrawal by the clinical study team and other specified reasons. Baseline characteristics of those missing a week 4 assessment for healthy vs. skin impaired volunteers, cream application vs. no barrier-enhancing cream and massaging vs. no massaging will be compared descriptively to those with complete follow-up at week 4. There will be no imputation for missing data.

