The European Union Horizon 2020-funded TRANS-FOODS project aims to understand the exact mechanisms behind transcutaneous sensitization and to develop and test novel prevention approaches. Here we present the protocol for an intervention study that forms part of the TRANS-FOODS programme of work to examine the immune responses to peanut allergens in individuals with and without AD, with and without skin massage. Specifically, we aim to determine whether peanut allergen components can penetrate the skin through regular massage and whether this effect is amplified in individuals with a compromised skin barrier. We will also investigate whether preapplication of a barrier-enhancing cream can reduce transcutaneous uptake of peanut proteins.

The primary objective of this study is to determine whether inflammatory cytokines, such as interleukin (IL)-4 and IL-13 can be detected in skin interstitial fluid (ISF) after regular massage using a peanut protein-containing extract.

The secondary objectives are:

To clarify whether this effect is amplified in those with an ­impaired skin barrier (patients with AD vs. healthy control ­p­articipants).To test whether peanut protein components present in skin ISF are able to induce activation of basophils in blood of ­donors allergic to peanuts.To assess whether the transcutaneous uptake of peanut protein can be reduced by the prior use of a barrier-enhancing cream.

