**Figure 1 vzag046-F1:**
[figure not shown]
Study flowchart: the peanut extract will be applied to the nondominant outer forearms of each participant, while the peanut extract vehicle will be applied as a control to the dominant forearm. Half of the participants will also have a barrier-enhancing cream applied to the nondominant forearm, 30 min prior to applying the peanut extract. Clinical and sample assessments will be taken at baseline and at week 4. AD, atopic dermatitis; IL, interleukin; TSLP, thymic stromal lymphopoeitin.

Samples of skin ISF will be collected from the control and intervention application sites. Transepidermal water-loss (TEWL) measurements will be taken from the inner forearm. SPT to peanut extract will be performed at baseline to ensure participants are not allergic to peanuts. All baseline measures will be repeated after the 4-week intervention period (Figure 1). Details of the study procedures are outlined below.

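### The AD (impaired-skin) main effect is estimated with baseline TEWL in the model, so it is the effect at equal TEWL and not the total effect of impaired skin

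*Protocol article*

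**What the plan says.** All references are to the Protocol article.

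- **Aim and objective** (introduction and list of objectives, under Protocol registration). The trial asks "whether this effect is amplified in individuals with a compromised skin barrier". The first secondary objective begins "To clarify whether this effect is amplified in those with an" impaired skin barrier, and identifies that contrast as patients with AD against healthy controls.
- **Model** (Statistical methods). The primary analysis is an ANCOVA for massage against no massage at week 4. "The terms in the model will include the effects of having impaired skin, use of barrier-enhancing cream and massage". The covariate sentence follows: "Covariates such as gender, ethnicity, baseline TEWL and baseline values of the outcome will be included, with TEWL considered a key mediating factor".
- **AD effect** (Statistical methods). "Secondary outcomes, including the effect of impaired skin, use of barrier-enhancing cream, and basophil and mast cell activation, and peanut-specific IgE levels, will be analysed" in a similar way to the primary outcome.
- **Interactions** (Statistical methods). They will be tested, "with significance levels set at 5% for main effects and 10% for interactions". Massage frequency is the only factor named; AD-by-massage is not named.
- **TEWL site** (text with Figure 1). "Transepidermal water-loss (TEWL) measurements will be taken from the inner forearm", whereas the Intervention section places the extract on the outer forearm.

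The text describes no model for the AD effect that leaves TEWL out.

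**The concern.** Baseline TEWL is a sound covariate for massage and cream. Both are randomized at the end of the baseline visit (Allocation), so a baseline value cannot be affected by them.

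AD is different. It is not randomized, it is present before baseline TEWL is read, and its role in the design is to represent a poor barrier. Baseline TEWL therefore lies on the path from AD to the outcome, and the protocol itself names TEWL as a mediator. Holding it fixed changes the question from whether impaired skin matters to whether AD matters among people whose barrier function is the same.

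What is at stake is how a secondary result is read. If the barrier carries much of the AD effect, the AD coefficient will be small for that very reason, and a reader could take it as evidence that impaired skin has little influence.

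**Working it through.** **The plan's figures.** The protocol states no AD effect, no AD-healthy TEWL gap and no mediated share, so there is no figure on this point to reproduce. Its sample-size statement (15 per group, over 90% power for a doubling) does reproduce: power is at least 0.995 for coefficients of variation of 8, 20 and 30%. It does not address the AD coefficient.

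**Inputs from the protocol.** Eight groups of 15 (2×2×2, N = 120), from Intervention. AD, cream, massage and baseline TEWL in one model, from Statistical methods.

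**Assumed inputs.** Total AD effect τ = 0.6 residual SD. TEWL gap d = 0.5, 1 or 1.5 SD. Share p of the AD effect carried by baseline TEWL = 25, 50, 75 or 100%. Two-sided 5% test (the protocol does not state sidedness). Gender, ethnicity and baseline cytokine are left out of the simulated model.

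**Step 1: algebra.** Let T = d·AD + e and Y = (1 − p)τ·AD + (pτ/d)·T + other terms.
- Without T in the model, the AD coefficient is (1 − p)τ + (pτ/d)·d = τ.
- With T in the model, it is (1 − p)τ. For τ = 0.6 this gives 0.45, 0.30, 0.15 and 0.

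**Step 2: simulation of the AD main effect, d = 1.**

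| Share p | AD without TEWL (SE; power) | AD with TEWL (SE; power) |
|---|---|---|
| 25% | 0.60 (0.184; 0.89) | 0.44 (0.205; 0.57) |
| 50% | 0.60 (0.190; 0.88) | 0.30 (0.205; 0.31) |
| 75% | 0.60 (0.200; 0.85) | 0.15 (0.206; 0.11) |
| 100% | 0.60 (0.213; 0.80) | 0.00 (0.206; 0.05) |

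The adjusted coefficients are nearly the same at d = 0.5 (0.46, 0.30, 0.15, 0.00) and d = 1.5 (0.45, 0.30, 0.14, 0.00).

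**Step 3: collinearity.** With two equal groups, adjusting for T multiplies the variance of the AD coefficient by 1 + d²/4, at a given residual variance. At d = 1 this is 1.25. It works against the gain from explaining outcome variance, which is why the standard error with TEWL is the larger one at low p and the smaller one only at p = 100%.

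**Step 4: AD-by-massage, assumed interaction 0.8 SD, d = 1.**

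| Share p | No TEWL | TEWL main effect only | TEWL and TEWL-by-massage |
|---|---|---|---|
| 25% | 0.81 | 0.81 | 0.61 |
| 50% | 0.79 | 0.79 | 0.39 |
| 75% | 0.83 | 0.83 | 0.24 |
| 100% | 0.79 | 0.79 | about 0 |

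Massage is randomized within AD and healthy participants, so a TEWL main effect is balanced across massage arms and leaves the interaction alone. A TEWL-by-massage term takes over the part of the interaction that runs through TEWL.

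**The case against.** **The amplification objective is an interaction.** A reader might infer that adjusting for TEWL defeats the stated objective. Step 4 shows that it does not: a TEWL main effect leaves AD-by-massage unbiased, and the protocol does not specify a TEWL-by-massage term. This objection stands and limits the point to the AD main effect. That effect remains in scope because Statistical methods lists the effect of impaired skin as an analysis of its own.

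**The mediator label.** A reader might also infer that the protocol treats baseline TEWL as a mediator of massage or cream, which a pre-randomization value cannot be. The text applies the label to TEWL in general, and TEWL is measured at both visits, so the documents do not make that claim. For AD, which precedes baseline TEWL, the label is coherent, and that coherence is what makes the adjustment a problem.

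**The covariate set may be open.** The list is introduced as examples and attached to the primary analysis, secondary analyses are only said to be similar, and the article is condensed. A fuller plan could separate the models. That is fair as to detail, but the one model described contains both terms.

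**The size is assumed.** The attenuation follows directly from the chosen share. A coefficient of zero needs baseline TEWL to capture the whole pathway. TEWL is read on the inner forearm and the extract goes on the outer forearm, and widespread AD, particularly at the forearm test sites, is excluded. Capture may well be partial and the TEWL gap small. This stands.

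**The TEWL coefficient would show the effect.** It would appear in the same model, so a careful reader need not be misled. That eases the consequence but does not supply the total AD effect.

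**Conclusion.** The point holds for the AD main effect. Followed as written, the plan reports AD against healthy at equal baseline TEWL, which is (1 − p) times the total effect. For an assumed total of 0.6 SD and a TEWL gap of 1 SD, that is about 0.44, 0.30, 0.15 or 0.00 at assumed shares of 25, 50, 75 or 100%, with power falling from 0.80–0.89 to 0.57, 0.31, 0.11 or 0.05. The direction follows from the model. The size cannot be known from the documents.

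The documents do not support the stronger conclusion that the trial would miss a true barrier effect. The massage and cream effects are unbiased, and AD-by-massage is unbiased unless a TEWL-by-massage term is added. Baseline cytokine, also a covariate, could absorb part of the AD effect in the same way; that is not quantified here. This should be corrected, but it does not threaten the primary analysis.

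**What to change.** Amend Statistical methods to state:

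1. Baseline TEWL stays as a covariate in the models for massage and cream.
2. The AD main effect is estimated in a model without baseline TEWL.
3. AD-by-massage is tested in a model without a TEWL-by-massage term. A TEWL main effect may remain there.
4. The TEWL-adjusted AD estimate is reported separately and labelled as an exploratory direct-effect (mediation) analysis.

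The cost is one additional model and no new data. The AD term may lose precision. In the simulation at a TEWL gap of 1 SD, its standard error is 0.184–0.213 without TEWL against 0.205–0.206 with it. At a gap of 0.5 SD the loss can be larger, up to 0.285 against 0.189 when TEWL carries the whole effect. Power for the AD effect is still higher without TEWL in every scenario run. The change is best made before the laboratory blind is lifted.

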**Methods:**

We report the study protocol for a single-site, observer blind randomized controlled trial, where healthy adults and adults with AD (*n* = 130) will be recruited and randomized, applying a peanut protein–containing extract to their outer forearm twice daily with/without massage and with/without a barrier-enhancing cream for a total of 4 weeks. The primary outcome is the potential detection of inflammatory cytokines in skin interstitial fluid (ISF), using a novel non-invasive ISF suction device. In addition, we will study whether the intervention enables detection of peanut protein components in retrieved skin ISF and results in increased transepidermal water-loss measurements.

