### Intervention

A total of 60 healthy adult volunteers and 60 adults with AD will be recruited and then randomized to ensure an even split between groups. A peanut protein extract will be used in all participants. The two groups will then be evenly split into the following groups through computer-generated randomization:

Group 1: application of the barrier-enhancing cream 30 min before application of the peanut protein extract ± massage after extract application.

Group 2: no application of the barrier-enhancing cream, just application of the peanut protein extract ± massage after extract application.

This will generate 8 intervention groups, each comprising 15 participants (outlined in Figure 1). Participants will wash their hands and forearms with soap and water before applying the test interventions to the central area of the nondominant outer forearm twice daily with a 5-min massage throughout the 4-week study period. The control formulation (with no protein extract) will be applied without massage to the central, dominant outer arm twice daily as the control. Clear instructions on the massaging technique will be given to all participants, which they will then follow at home using video guidance. Standardized instructions, demonstration videos and written guidance will be used to promote consistent technique and frequency across participants, with weekly text reminders to reinforce adherence and reduce interparticipant variability. Adherence will be monitored using daily record surveys.

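### Interaction tests on massage frequency use a variable that the design holds at one assigned level, so beyond massage yes/no they compare self-selected adherence groups

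*Protocol article*

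**What the plan says.** All places are in the protocol article.

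- **Abstract, Methods.** The extract is applied "twice daily with/without massage and with/without a barrier-enhancing cream for a total of 4 weeks". Massage is a yes/no factor and twice daily is the only rate given.
- **Intervention.** The cream arm is described as "application of the barrier-enhancing cream 30 min before application of the peanut protein extract ± massage after extract application", and the no-cream arm has the same massage split. Application is "twice daily with a 5-min massage throughout the 4-week study period". The section adds: "This will generate 8 intervention groups, each comprising 15 participants". Instructions, videos and reminders are meant to keep technique and frequency alike across participants, and adherence is recorded in daily surveys.
- **Statistical methods.** The primary analysis is an ANCOVA of massage against no massage "by intention-to-treat at week 4". Its listed terms are impaired skin, cream and massage, plus covariates. After the sentence on secondary outcomes comes: "Interaction effects, including those involving massage frequency (categorical and continuous), will also be tested". The levels for these tests are 10% for interactions, as against 5% for main effects. The article does not say what massage frequency is measured by, and does not mark these tests as exploratory or observational.

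**The concern.** The plan commits to testing a factor that the design deliberately keeps constant. Since there is one non-zero assigned level, any further spread in frequency arises after randomization from participants' own behaviour. The only stated record of that behaviour is the self-completed daily survey.

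A test of whether the frequency effect differs between AD and healthy skin, or with and without cream, then inherits whatever makes people massage more or less. If, for example, irritated skin led to less massage and also to higher cytokines, mainly in AD, the frequency-by-AD term would pick this up even if massage did nothing. Whether the massage effect is amplified in AD is the first secondary objective, so a false signal there would bear on a named question of the trial.

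**Working it through.** **1. Levels of frequency in the design.** Skin type (2) × cream (2) × massage (2) = 8 groups, which reproduces the article's count, and 8 × 15 = 120 participants. Half are assigned massage: 60, or 30 AD and 30 healthy. Assigned frequencies are zero (no massage) and twice daily (massage). The only randomized frequency contrast is therefore massage yes/no, which the model already contains as massage. A categorical variable with more than two levels, or a continuous one, must draw on adherence.

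**2. Size for a frequency-by-AD interaction, by Fisher's z.** The correlation between reported frequency and cytokine level is an assumption; the article gives none. Comparing the correlations of the two skin groups approximates the interaction test.

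- Standard error of the difference: √(1/(30−3) + 1/(30−3)) = √(2/27) = 0.272.
- Correlation −0.3 in AD only: atanh(0.3) = 0.3095, and 0.3095/0.272 = 1.14. Two-sided rejection at 10%: Φ(1.14 − 1.645) + Φ(−1.14 − 1.645) ≈ 0.31.
- Correlation −0.2 in AD only: 0.2027/0.272 = 0.745, so Φ(−0.90) + Φ(−2.39) ≈ 0.19.
- Correlation −0.4 in AD only: 0.4236/0.272 = 1.557, so Φ(−0.09) + Φ(−3.20) ≈ 0.47.
- The same correlation in both skin groups: the expected difference is zero, so rejection is about 10%.

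The inflation depends on the adherence–prognosis link differing between the groups compared.

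**3. Simulation of the interaction test.** Assumed: 120 participants, no massage effect at all, and a latent trait that drives adherence in everyone but the outcome in AD only. There were 3,000 runs per setting. The categorical version used none, low and high frequency. Rejection of the AD interaction at nominal 10%:

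| Effect of the trait on outcome in AD (SD) | 0 | 0.3 | 0.5 | 0.8 |
|---|---|---|---|---|
| Observed frequency, categorical | 10% | 18% | 32% | 57% |
| Observed frequency, continuous | 10% | 11% | 14% | 17% |
| Assigned massage arm | 11% | 10% | 9% | 10% |

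The continuous version inflates less, plausibly because it includes the no-massage participants at zero, so much of its spread is the randomized contrast. The assigned-arm test stays near 10% throughout. These inputs are assumptions and show direction only.

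**The case against.** **The analysis plan may define the variable.** A condensed article can leave the definition, data source and cut-points to the analysis plan, so their absence is not the point. What the article does state is a test on a factor that its own design fixes. A later definition could only equate frequency with adherence or reduce it to massage yes/no. The yes/no reading does not fit a continuous form.

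**The mechanism is conjecture.** This stands. Nothing in the article supports a particular correlation or irritation-driven non-adherence. Widespread AD is excluded, particularly at the test sites, the study is called low risk, and reminders aim at uniform frequency. The irritation example would also give an inverse dose response, which would not lend support to a massage effect. The figures above are therefore illustrations.

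**Dose-response analyses by adherence are legitimate.** This also stands, and the article does not call these tests randomized comparisons. The issue is their unlabelled place among the inferential interactions, under the same significance rule.

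Three stronger readings are tempting and are not supported:

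- A reader might infer that frequency enters the intention-to-treat model and changes the meaning of the massage coefficient. The article attaches intention-to-treat only to the primary comparison and does not list frequency among that model's terms.
- A reader might infer that a massage-by-frequency term is planned, which could not be separated from a frequency slope within the massage groups. No such term is named; frequency by AD and frequency by cream are the natural reading, and both can be estimated.
- A reader might take a correlation of −0.3 among all 60 massage participants, get atanh(0.3) × √57 = 2.34, and conclude that a false result at 10% occurs Φ(2.34 − 1.645) = 76% of the time. That is a main association judged at the level the article reserves for interactions, so it matches no planned test.

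**Conclusion.** The point holds in a limited form. The article plans interaction tests on massage frequency although it assigns one frequency. Beyond massage yes/no, those tests rest on self-reported adherence after randomization and are open to confounding. For frequency by AD, rejection at nominal 10% is about 31% if a correlation of −0.3 exists in AD only (19% to 47% for −0.2 to −0.4), and about 10% if the correlation is equal in both skin groups. These values assume 30 massage participants per skin group and no true effect of frequency. The primary massage comparison and the sample size are untouched as written. It is worth correcting before analysis, but it does not threaten the main result.

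**What to change.** In Statistical methods, base the inferential interaction tests on the assigned massage factor:

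- massage by cream, where both factors are randomized;
- massage by AD, described as a subgroup comparison of a randomized effect, because AD status is not randomized.

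Move massage frequency to a supplementary adherence analysis within the massage groups, with one prespecified definition taken from the daily survey, and label it observational. A complier-average effect with assigned massage as the instrument could be added, but it answers a different question and is optional.

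The cost is wording only, since the adherence data are already collected. The downside is that the frequency dose-response loses inferential status.
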